## Study Protocol for All Admission Surveillance (6/8/2016)

### Background

*Clostridium difficile* infection (CDI) remains a constant, even increasing, clinical infection threat in the United States and Europe. New preventive strategies are urgently needed. Current control measures do not target asymptomatic carriers, despite evidence that they can contaminate the hospital environment and health care workers' hands; a risk to potentially transmit *C. difficile* to other patients. Of special importance is that not only is disease prevalence increasing, but severity of illness and mortality also is on the rise. We have implemented many intervention practices at our healthcare system including bleach cleaning of rooms with CDI patients, monitoring of environmental services' room cleaning, hand hygiene education and even UV light disinfection of rooms harboring CDI patients. To date, none have been consistently effective. We believe that CDI is much like MRSA, in that many more patients are colonized than infected, and one (perhaps the optimal) way to curtail disease is to interrupt transmission by identifying carriers and placing them into contact (glove and gown) precautions.

We propose to test this hypothesis with a quality improvement program initiative at NorthShore. Our primary goal is to demonstrate that surveillance testing for *C. difficile* colonization at the time of admission and contact precaution isolation of those positive will reduce spread of the organism as well as lower clinical CDI. Our secondary goal is demonstrate that such a program is cost effective.

The primary outcome measure is reduced CDI disease. The secondary outcome measures are reduced cost for the care of patients with CDI (by avoiding disease) and meeting CMS threshold criteria for CDI disease rates in our acute care facilities.

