### Study Methods

We have collected CDI disease rates for 10 years. One of our hospitals admits a high number of patients from long term care facilities (LTCFs) and currently has a hospital-onset (HO) CDI rate of 1.1 cases/1,000 patient days. The figure below presents their CDI data for calendar 2015, and the nosocomial CDI rate at this facility has been rising during the first quarter of 2016. The hospital admits 25 patients per day, which translates to 2,250 admission tests in 3 months, and for this facility represents approximately 11,000 patient days. We plan to introduce perirectal (intra-anal) swab testing for *C. difficile* on all admissions for 3 months, accompanied by isolation of positive patients, which we hypothesize will lower the rate to 0.3 cases/1,000 patient days. In absolute numbers, the goal is to reduce the rate from 4 nosocomial cases per month down to 1 nosocomial case per month. This will provide a sample size that can demonstrate a level of significance at  $p < .05$  for disease reduction with the intervention when compared to the time frame prior to the admission testing intervention. The testing period can be extended if we have not reached the estimated number of consenting patients within the first 3 months of the planned program.

Those patients positive will be placed into contact precaution isolation (gown and gloves worn by all healthcare workers). We will be collecting a double headed swab (Culturette) on all patients, so those testing positive will also have the second swab cultured for *C. difficile* that will be archived for further testing. We will also validate the procedure by culturing a similar number of patients who have a negative Roche C. Diff Cobas test (the first negative patient tested after each positive *C. difficile* result).

As a supplemental data set, our system implemented all hospital inpatient point prevalence surveys (rectal swabs) for CDI and MDRO Gram negative bacteria in the month of June 2016.

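### The protocol's only cost outcome counts CDI care avoided and leaves out the cost of screening and isolation, so it cannot answer the stated cost-effectiveness goal

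*Protocol*

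**What the plan says.** The Background section of the protocol states the economic aim in one sentence: "Our secondary goal is demonstrate that such a program is cost effective". The paragraph that follows names two secondary outcomes. One is "reduced cost for the care of patients with CDI (by avoiding disease". The other is "meeting CMS threshold criteria for CDI disease rates in our acute care facilities", which is a rate criterion and not a cost.

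The resources that the program consumes are described elsewhere, without any cost attached:

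- Study Methods gives the testing volume ("The hospital admits 25 patients per day, which translates to 2,250 admission tests in 3 months") and places every patient who tests positive under gown-and-glove precautions.
- Study Period assigns swab collection to admitting nurses or patient care technicians.
- Testing Plan has the assay run at the central hospital six days a week.

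No section prices these resources, sets them against the savings, or defines a net cost or a cost per case averted.

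**The concern.** Cost-effectiveness compares what a program costs with what it achieves. The named outcome measures only part of what is achieved, namely treatment cost avoided. At any given cost per CDI case it is positive as soon as one case is averted, and it does not change whether the screening was cheap or expensive. Goal and outcome are both fixed in the protocol and do not match, so an analysis that follows the named outcome faithfully would still leave the goal unanswered.

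The gap also matters for a question that the protocol raises itself. Testing Plan anticipates that wider deployment might test only selected admissions. All-admission and targeted screening differ mainly in the number of tests and isolations, and a savings-only measure gives no credit for tests and isolation days that are spared.

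**Working it through.** **Inputs (all from Study Methods unless noted)**

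- 25 admissions per day for 3 months, taken as 90 days.
- About 11,000 patient days in the same period ("represents approximately 11,000 patient days").
- Baseline rate 1.1 per 1,000 patient days ("currently has a hospital-onset (HO) CDI rate of 1.1 cases/1,000 patient days") and target rate 0.3 ("which we hypothesize will lower the rate to 0.3 cases/1,000 patient days"), restated there as 4 cases per month falling to 1.
- Admission prevalence of 5%, which the protocol offers as an example only.
- Unit costs: none in the document.

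**Step 1: reproduce the protocol's figures**

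- Tests: 25 × 90 = 2,250, as stated.
- Cases before: 1.1 × 11,000 / 1,000 = 12.1 per 3 months, or 4.0 per month.
- Cases after: 0.3 × 11,000 / 1,000 = 3.3 per 3 months, or 1.1 per month.
- Cases averted: 12.1 − 3.3 = 8.8 from the rates, or (4 − 1) × 3 = 9 from the monthly counts.

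The stated volumes are consistent with each other.

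**Step 2: resources that the cost outcome omits**

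- Tests per averted case: 2,250 / 9 = 250 (2,250 / 8.8 = 256).
- Mean stay: 11,000 / 2,250 = 4.9 days.
- Patients isolated at 5%: 2,250 × 0.05 = 112.5, about 113.
- Isolation days, if every such patient is isolated for the whole mean stay: 112.5 × 11,000 / 2,250 = 550.
- Isolation days per averted case: 550 / 9 = 61 (550 / 8.8 = 62.5).

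If only half the effect is achieved (4.5 cases averted), the ratios double to 2,250 / 4.5 = 500 tests and 550 / 4.5 = 122 isolation days per averted case. The totals of 2,250 tests and 550 days do not change, because they depend on admissions, prevalence and stay and not on cases averted.

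**Step 3: why the outcome cannot discriminate**

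Let t be the cost per test, d the cost per isolation day and c the care cost per CDI case.

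- Named outcome: 9c. It contains neither t nor d.
- Net cost, before staff time for swabs: 2,250t + 550d − 9c.
- Break-even: c = 250t + 61.1d.

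For illustration only, assume t and d each lie between 20 and 100 currency units. At the low end, program cost is 2,250 × 20 + 550 × 20 = 56,000 and break-even is 56,000 / 9 = 6,222 per case. At the high end they are 280,000 and 31,111. The named outcome is the same 9c throughout. Break-even marks cost neutrality; a program may cost more than it saves and still be judged cost effective, but that judgement too needs t and d.

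**Step 4: precision of a cost per case averted**

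Assume 12 and 3 cases in two equal 3-month periods and independent Poisson counts. The difference is 9 with standard error √(12 + 3) = 3.87, so an approximate 95% interval is 9 ± 1.96 × 3.87, or 1.4 to 16.6 cases. Tests per averted case then range from 2,250 / 16.6 = about 136 to 2,250 / 1.41 = about 1,600. The protocol does not fix the length of the comparison period; a longer baseline would narrow this interval.

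**The case against.** The strongest reply is that the protocol is brief and that cost components, perspective and method are commonly left to an analysis plan, which is not at hand here. The protocol does not exclude program costs, and it does not say that savings in CDI care will by themselves establish cost-effectiveness. This stands as far as it goes: a plan could add the missing costs. It does not remove the mismatch, because goal and outcome are written side by side in the protocol and the outcome as named does not serve the goal.

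Several stronger readings are tempting, and the document does not support them.

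- A reader might infer that a savings-only result will be used to justify extension to all four hospitals. Potential Benefit ties extension to the pilot's success and gives reduced hospital-onset CDI as the main objective; cost is not mentioned there.
- A reader might take 12% as an upper bound for positive admissions. That figure is a past inpatient point prevalence. Study Methods treats an admission prevalence below it as the sign of in-hospital spread, so pairing 12% at admission with the full effect would go against the protocol's own reasoning.
- A reader might count the cultures as program cost. Study Methods describes them as archiving and validation, so they are study costs.

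The 550 isolation days are an upper figure at 5% prevalence. Samples go to a central laboratory six days a week, so isolation prompted by a result would start some time into the stay, and carriers need not have the average stay.

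**Conclusion.** The concern holds as a mismatch between a stated goal and the outcome named to serve it. Followed as written, the cost outcome would show a saving for any fall in CDI and could not establish cost-effectiveness.

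The figure of about 250 tests per averted case rests only on the protocol's own volumes and its hypothesised effect. The figure of up to 550 isolation days, about 61 per averted case, rests in addition on the illustrative 5% prevalence and on isolation for the full mean stay. The mismatch itself depends on neither of these, nor on any unit cost.

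Whether the program is in fact cost effective cannot be judged from the document, and nothing here suggests that it is not. The point should be corrected, but it concerns a secondary goal and leaves the primary outcome and its test as they are.

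**What to change.** Redefine the secondary cost outcome as net program cost: admission tests, swab-collection time and contact-precaution days, minus CDI care cost avoided. Report it also per hospital-onset CDI case averted. State the range over which unit costs are varied, and show the uncertainty of the rate difference alongside the result. Report the archive and validation cultures separately as study costs.

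The alternative is to restate the secondary goal as savings in CDI care and make no cost-effectiveness claim. That needs only a change of wording.

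The first option requires a tally of tests, collection time and isolation days, together with unit costs that the protocol does not give. The cost result may look less favourable, and with so few cases the cost per case averted will be imprecise, so net cost should be shown beside the ratio. Neither option changes any patient procedure.

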### Study Methods

We have collected CDI disease rates for 10 years. One of our hospitals admits a high number of patients from long term care facilities (LTCFs) and currently has a hospital-onset (HO) CDI rate of 1.1 cases/1,000 patient days. The figure below presents their CDI data for calendar 2015, and the nosocomial CDI rate at this facility has been rising during the first quarter of 2016. The hospital admits 25 patients per day, which translates to 2,250 admission tests in 3 months, and for this facility represents approximately 11,000 patient days. We plan to introduce perirectal (intra-anal) swab testing for *C. difficile* on all admissions for 3 months, accompanied by isolation of positive patients, which we hypothesize will lower the rate to 0.3 cases/1,000 patient days. In absolute numbers, the goal is to reduce the rate from 4 nosocomial cases per month down to 1 nosocomial case per month. This will provide a sample size that can demonstrate a level of significance at  $p < .05$  for disease reduction with the intervention when compared to the time frame prior to the admission testing intervention. The testing period can be extended if we have not reached the estimated number of consenting patients within the first 3 months of the planned program.

Those patients positive will be placed into contact precaution isolation (gown and gloves worn by all healthcare workers). We will be collecting a double headed swab (Culturette) on all patients, so those testing positive will also have the second swab cultured for *C. difficile* that will be archived for further testing. We will also validate the procedure by culturing a similar number of patients who have a negative Roche C. Diff Cobas test (the first negative patient tested after each positive *C. difficile* result).

As a supplemental data set, our system implemented all hospital inpatient point prevalence surveys (rectal swabs) for CDI and MDRO Gram negative bacteria in the month of June 2016.

If we assume that this proposed program can begin shortly after the new point prevalence NorthShore program, we will have before and after point prevalence data to demonstrate reduction in transmission. In the past we have found the point prevalence of *C. difficile* at the target hospital to be 12% of inpatients. Thus, for example, if the admission prevalence is 5% this would demonstrate that there is considerable spread of *C. difficile* in the hospital after admission. If the proposed admission screening program is successful, we might expect the second point prevalence (planned for September) to be reduced to the same rate as the admission prevalence because we have prevented spread. If this is found, we will have demonstrated that both transmission and disease are reduced by implementing the admission screening program. This limitation of this supplemental analysis is that the number of patients sampled and the rate of positive results may be too small to reach a valid threshold for analysis.

Statistical significance will be determined using the Chi Square/Fisher exact test, with  $p \leq 0.05$  being required to determine significance.

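### A gap between inpatient point prevalence (12%) and admission prevalence (for example 5%) does not by itself demonstrate or size in-hospital spread, because only the survey weights patients by length of stay

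*Protocol*

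**What the plan says.** All of this stands in the Protocol, Study Methods, unless noted.

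- Past surveys found the point prevalence of *C. difficile* "at the target hospital to be 12% of inpatients".
- The inference from that figure is that "if the admission prevalence is 5% this would demonstrate that there is considerable spread of" the organism in hospital. The 5% is an example; admission prevalence was not yet known.
- If the programme works, the September survey is expected "to be reduced to the same rate as the admission prevalence because we have prevented spread".
- If that is found, the stated conclusion is that "we will have demonstrated that both transmission and disease are reduced by implementing the admission screening program".
- The one limitation named for this analysis is that "the number of patients sampled and the rate of positive results may be too small to reach a valid threshold for analysis".

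The two prevalences come from different samples. Each admission is swabbed once, on arrival (Testing Plan). The surveys of June and September swab the inpatients then in hospital. Study Methods calls the survey data supplemental. Background puts reduced spread of the organism in the primary goal, while the primary outcome measure is CDI disease.

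**The concern.** Admission prevalence gives every admission equal weight. A survey gives a patient who stays ten days ten times the chance of being present that a one-day patient has. If those already colonised on arrival also tend to stay longer, they are over-represented in the survey, and point prevalence exceeds admission prevalence even when nobody acquires the organism in hospital. The target hospital takes many patients from long-term care, so such a link is plausible, but the Protocol reports no length of stay by carriage status.

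Two readings are at stake. A 12% v 5% gap could be called considerable spread when part or all of it reflects who is in the beds. In the other direction, a programme that stopped all spread could appear to fall short because point prevalence remained above the admission rate. The stated limitation does not cover this: a larger survey reduces random error but leaves the bias in place.

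The final conclusion also reaches disease, although its stated condition is a carriage result alone.

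**Working it through.** **Inputs from the Protocol (Study Methods).** Point prevalence 12%; example admission prevalence p = 5%; 25 admissions a day and 2,250 in 3 months; about 11,000 patient days in the same period.

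**The plan's own figures.** 25 × 90 = 2,250, as stated. Mean stay is 11,000 / 2,250 = 4.89 days. Mean census is 11,000 / 90 = about 122.

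**Assumed input.** r = mean stay of admission carriers divided by mean stay of non-carriers. The documents do not give it, so a range is shown.

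**Formula.** In steady state with no acquisition in hospital:

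point prevalence = p·r / (p·r + 1 − p)

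| r | Calculation | Point prevalence, no spread | Share of the 7-point gap |
|---|---|---|---|
| 1 | 0.050 / 1.000 | 5.0% | 0% |
| 1.5 | 0.075 / 1.025 | 7.3% | 33% |
| 2 | 0.100 / 1.050 | 9.5% | 65% |
| 2.5 | 0.125 / 1.075 | 11.6% | 95% |
| 3 | 0.150 / 1.100 | 13.6% | more than 100% |

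**Ratio that reproduces the whole gap.** r = (0.12/0.88) / (0.05/0.95) = 2.59. At the overall mean of 4.89 days, non-carriers stay 4.89 / (0.95 + 0.05 × 2.59) = 4.5 days and carriers 2.59 × 4.53 = 11.7 days. A simulation of 2,000,000 stays with these means and no acquisition gave 12.0%.

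**If the link runs only through long-term care.** Let a share s of admissions come from long-term care, with carriage a and k times the stay of the rest, and no link between carriage and stay within either group. The others then have carriage b = (0.05 − s·a)/(1 − s), and point prevalence is (s·k·a + (1 − s)·b)/(s·k + 1 − s). All three inputs are assumptions.

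- s = 10%, a = 10%, k = 1.5: (0.015 + 0.040)/1.05 = 5.2%.
- s = 20%, a = 25%, k = 3 (so b = 0): 0.150/1.40 = 10.7%.

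These were the lowest and highest results over s of 10–30%, a of 10–25% and k of 1.5–3. None reached 12%.

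**Sampling error on top.** The size of the past survey is not given. With 122 patients (assumed), 15 positives (12.3%) has a 95% interval of about 7.6% to 19.3%. With no spread, the chance of 15 or more positives is 0.1% at r = 1, 3.3% at r = 1.5 and 18% at r = 2.

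**The September benchmark.** The admission rate is the no-spread value of point prevalence only when r = 1. At r = 2, a programme that stopped all acquisition would leave 9.5% in the survey against 5% at admission.

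**The case against.** The strongest reply is that long-stay sampling alone produces no gap. Carriers must also stay longer, and by a ratio of about 2.6 to explain everything. The documents give no such ratio, and a long-term-care intake does not fix one. This stands. A reader might infer from the table that the 12% v 5% gap is an artefact and that spread is absent; the documents do not support that. Nor do they support saying that a perfect programme could never reach the admission rate: at a ratio of 1 it would.

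Second, the before-and-after evidence on transmission is introduced as survey against survey. June and September are length-biased in the same way, so with stable case mix and stay the bias largely cancels. This also stands. A reader might conclude that all the transmission evidence is void, which goes too far.

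Third, the 5% is only an example, the fall to the admission rate is an expectation with no test tied to it, the analysis is supplemental, and no listed outcome measures carriage. This limits the stakes. It does not rescue the wording: the Protocol says that the gap would demonstrate spread and that meeting the benchmark would demonstrate the programme's effect, and it never mentions stay.

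Fourth, an admission-negative, survey-positive pair is not proof of acquisition. The surveys use rectal swabs with no assay stated, whereas admission uses a perirectal swab on an assay the study itself sets out to validate. This stands and is carried into the fix.

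**Conclusion.** The concern holds in a limited form. The contrast between point and admission prevalence is compatible with in-hospital spread but does not by itself establish or size it. With 5% at admission and no acquisition, the survey figure would be 5.0% at a stay ratio of 1, 7.3% at 1.5, 9.5% at 2 and 12.0% at about 2.6. Ratios of 1.5 to 2 would thus account for about one to two thirds of the gap. With any ratio above 1, equality with the admission rate is also the wrong mark of success.

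This rests on an assumed stay ratio, steady state and the example value of 5%. The June v September comparison is less affected if case mix and stay are stable, and the primary CDI outcome is not affected. Separately, a carriage result alone cannot support the conclusion that disease is reduced; the CDI rates have to show that.

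**What to change.** - **September.** Compare the survey results with the same surveyed patients' own admission swabs, which are already planned. This removes the mismatch of denominators. Report the share admission-negative and survey-positive, by days since admission, as *apparent* acquisition. State that missed carriage at admission, and any difference in swab or assay, can contribute.
- **Before and after.** Make June v September the main contrast, stratified by days since admission.
- **Wording.** Say that a gap *would be compatible with* spread; add length-of-stay bias to the stated limitations; delete disease from what the prevalence result is said to demonstrate.

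The cost is record linkage, which needs survey results that can be matched to patients, and some rewording; no extra swabs are needed. Three drawbacks remain. June has no admission swabs, so apparent acquisition is available only for the programme period. With a census near 122, few conversions are likely. Precision of the main contrast is also low: with 122 patients in each survey (assumed), a fall from 12% to 5% would be detected with about 50% power at a two-sided 5% level.

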### **Study Period**

The planned study period is 3 months - an extension for an additional 6 months can occur based on the initial 3 month data analysis. All admissions to the target hospital will be tested, and the program will continue until at least 2,000 patients have taken part. There are no exclusion criteria. The Department of Nursing has agreed that admitting nurses or patient care technicians (PCTs) will collect the perirectal swab sample specimen.

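### A 6-month extension may follow the 3-month data analysis with no stated criterion and one unadjusted 0.05 threshold; testing CDI at both 3 and 9 months can push the type I error above 5%

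*Protocol*

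**What the plan says.** The protocol has two extension triggers and one significance rule.

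- **Protocol, Study Period.** The planned duration is 3 months, and "an extension for an additional 6 months can occur based on the initial 3 month data analysis". No endpoint, criterion or direction of result is attached. The same section separately sets a floor of 2,000 participants.
- **Protocol, Study Methods, on accrual.** "The testing period can be extended if we have not reached the estimated number of consenting patients within the first 3 months". This trigger concerns enrolment only.
- **Protocol, Study Methods, on significance.** "Statistical significance will be determined using the Chi Square/Fisher exact test", with p at or below 0.05 "being required to determine significance". No interim look, no division of alpha and no designated confirmatory analysis is mentioned.

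The 3-month period is sized on the primary outcome. The hospital "currently has a hospital-onset (HO) CDI rate of 1.1 cases/1,000 patient days", and the intervention is one "which we hypothesize will lower the rate to 0.3 cases/1,000 patient days". In counts, the aim is to "reduce the rate from 4 nosocomial cases per month down to 1 nosocomial case per month". This is said to be enough for significance "for disease reduction with the intervention when compared to the time frame prior to the admission testing intervention".

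**The concern.** The 3-month period is planned so that a significant CDI reduction could be shown at its end. The protocol also lets the study run for a further 6 months depending on what the 3-month analysis shows. Nothing in it says that a non-significant 3-month test uses up any of the 5%, or that a significant one would be provisional. A team could declare success at 3 months if p is at or below 0.05, and otherwise extend and test the accumulated data at the same level. That gives chance two opportunities.

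The path is not remote. At the hypothesised rates the power at 3 months is only about 54-63%, so a missed first test followed by an extension is likely even if the intervention works.

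Having two triggers adds a further difficulty. After the fact, a reader could not tell whether an extension was driven by accrual or by the result.

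**Working it through.** **Inputs.** From Study Methods: baseline rate 1.1 and target rate 0.3 per 1,000 patient-days; about 11,000 patient-days in 3 months; 4 versus 1 cases per month; chi-square or Fisher exact test at 0.05. From Study Period: 3 months, then possibly 6 more.

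Not given, so assumed: two-sided testing (one-sided also run); a baseline of 3 months, of 12 months (calendar 2015), or matched to the intervention period (3 then 9 months); Poisson counts at a constant rate with no effect. The monthly count is 1.1 × 11 / 3 = 4.03.

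**Step 1: the plan's own figure.** Three months at 4 and 1 per month give 12 versus 3 cases, each over 11,000 patient-days. Fisher p = 0.035 two-sided, Pearson p = 0.020, Yates p = 0.039. The claim of p < .05 therefore reproduces at the expected counts. Power is lower than this may suggest: 54% (Fisher) to 63% (Pearson) by exact enumeration.

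**Step 2: normal theory for two looks.** Let the pre-intervention period be b months, with intervention data at 3 and 9 cumulative months. Under a common rate, the variance of the rate difference is proportional to 1/b + 1/t. With a fixed baseline shared by both looks, the correlation of the two test statistics is

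ρ = √[(1/b + 1/9) / (1/b + 1/3)].

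- b = 3: √(0.4444/0.6667) = 0.816
- b = 12: √(0.1944/0.4167) = 0.683
- matched baseline: √[(2/9)/(2/3)] = 0.577

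The overall type I error is 1 − P(|Z₁| < 1.96 and |Z₂| < 1.96), with Z₁ and Z₂ bivariate normal with correlation ρ. This gives 7.7%, 8.4% and 8.8% respectively. Independent looks would give 1 − 0.95² = 9.75%, an upper reference.

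**Step 3: actual small counts.** The rule is: claim success if p ≤ 0.05 at 3 months, otherwise extend and test all 9 months at p ≤ 0.05. The Fisher-type test conditions on the total count.

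| Baseline | Pearson chi-square | Fisher-type exact | Yates |
|---|---|---|---|
| 3 months | 7.9% | 5.6% | 4.8% |
| 12 months | 8.2% | 7.3% | 6.0% |
| Matched | 9.2% | 6.1% | 5.9% |

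With one-sided 0.05 at each look, the figures are 7.7-8.6% (Pearson) and 5.4-6.4% (Fisher-type).

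**Step 4: other rules the wording would allow** (two-sided).

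| Decision rule | Pearson | Fisher-type |
|---|---|---|
| Always extend, test once at 9 months | 4.8-5.1% | 3.8-4.5% |
| Extend only if the rate is lower but not significant | 6.6-7.2% | 4.5-5.8% |

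Extending only after a significant 3-month result, and requiring significance again at 9 months, gives 0.7-2.3% across both tests.

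**Step 5: a split that holds 5%.** With p ≤ 0.005 at 3 months, the critical p at 9 months by normal theory is 0.0491 for a 3-month baseline and 0.0470 for a matched one. A final level of 0.047 therefore holds the total at about 5% across the baselines considered. A constant level per look of about 0.032, 0.029 or 0.028 (3-month, 12-month, matched) would also do so.

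**The case against.** The strongest reply is that the protocol never says what this concern needs it to say. A reader might infer that the CDI result decides the extension, that 0.05 is applied at each analysis, and hence that the false-positive rate does exceed 5%.

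- **The outcome reading.** Study Period refers only to a data analysis and names no endpoint. It is a fair inference: CDI is the primary outcome, the 3 months are sized on it, and accrual is handled in a separate sentence. It remains an inference.
- **Repeated use of 0.05.** This is read from silence. One threshold is given and two primary tests are not described. Alpha allocation is often placed in an SAP, which is not at hand.
- **Size.** The inflation depends on the decision rule, the test and the baseline. Some compatible rules give none, and a conservative test absorbs much of it.
- **The two triggers.** Both are permissive and could operate side by side. They are inconsistent, but neither excludes the other.

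These replies stand, and they rule out a flat statement that the error exceeds 5%. They do not remove the point. The protocol itself, not only an absent SAP, ties continuation to a data analysis without a criterion, beside an accrual trigger and an undivided threshold. An SAP could allocate alpha, but the protocol would still carry two different triggers.

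**Conclusion.** The point holds as a conditional one. The protocol permits result-dependent continuation and a second test, and contains nothing that controls the error if that happens. If CDI is tested at two-sided 0.05 at 3 months and, when not significant, again at 9 months, the type I error is about 8-9% with chi-square and about 5-7% with a Fisher-type exact test. The protocol names both tests without choosing. Only Yates correction with a 3-month baseline stays below 5% on this path, and the protocol does not mention that correction.

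The stronger conclusion, that the stated 5% is necessarily breached, is not supported: an extension driven by accrual alone, or one test at the end, would leave it essentially intact.

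The figures assume Poisson counts, a constant rate of 1.1 per 1,000 patient-days and no secular trend. Study Methods reports a rising rate in early 2016, and these figures do not capture that.

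**What to change.** Reconcile Study Methods and Study Period so that one extension rule governs, in one of two ways.

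1. **Preferred.** Let extension depend only on accrual or patient-days, not on the CDI result. State that there is one confirmatory test, at the end, on the whole intervention period. This costs only a change of wording. It gives up a confirmatory claim at 3 months if the study is extended.
2. **If a 3-month efficacy look is wanted.** Say so, state the result that leads to extension, and divide alpha. One example is p ≤ 0.005 at 3 months and p ≤ 0.047 at 9 months on the pooled 9 months; other valid splits exist. The cost is that the expected 12 versus 3 result (Fisher p = 0.035) would not support an early success claim at 3 months.

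Under either option, fix the length of the baseline period, since the size of the error depends on it.
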